## Abstract

**Background:**

Local corticosteroid injection for carpal tunnel syndrome (CTS) provides greater clinical improvement in symptoms one month after injection compared to placebo but significant symptom relief beyond one month has not been demonstrated and the relapse of symptoms is possible.

Neuroprotection and myelin repair actions of the progesterone was demonstrated in vivo and in vitro study.

We report the design of a randomized controlled trial for the local injection of cortisone versus progesterone in "mild" idiopathic CTS.

**Methods:**

Sixty women with age between 18 and 60 years affected by "mild" idiopathic CTS, diagnosed on the basis of clinical and electrodiagnostic tests, will be enrolled in one centre. The clinical, electrophysiological and ultasonographic findings of the patients will be evaluate at baseline, 1, 6 and 12 months after injection.

The major outcome of this study is to determine whether locally-injected progesterone may be more beneficial than cortisone in CTS at clinical levels, tested with symptoms severity self-administered Boston Questionnaire and with visual analogue pain scale.

Secondary outcome measures are: duration of experimental therapy; improvement of electrodiagnostic and ultrasonographic anomalies at various follow-up; comparison of the beneficial and harmful effects of the cortisone versus progesterone.

**Conclusion:**

We have designed a randomized controlled study to show the clinical effectiveness of local progesterone in the most frequent human focal peripheral mononeuropathy and to demonstrate the neuroprotective effects of the progesterone at the level of the peripheral nervous system in humans.

## Introduction

Fifty years after its widespread recognition, a significant minority of patients with carpal tunnel syndrome continue to experience poor outcomes from treatment. Much of the current treatment is supported by inadequate or nonexistent evidence. Surgical decompression, often considered the definitive solution, leads to positive results in 75% of the cases, but leaves 8% of patients worse than before [1].

Open release is the preferred surgical procedure. Some patients referred failure to relieve symptoms after decompression surgery, and reoperation is sometimes necessary. This is consequence of incomplete release of the flexor retinaculum, scarring around the median nerve, or incorrect diagnosis [2-4]. Open release is not without complications, these produce symptoms different from those present before surgery and can be very disabling and difficult to treat. The "major" complications are rare and consists in lesion of the recurrent motor branch, severance of the palmar cutaneous branch of the median nerve or of palmar terminal branches of the median or ulnar nerves with or without neuroma, bowstringing of the flexor retinaculum, tendon or artery injuries, reflex sympathetic dystrophy. The "minor" complication are more frequent (pillar pain, loss of grip, scar tenderness or hypertrophy, wound infection, trigger finger) [5-7].

Pillar pain and loss of grip are temporary and spontaneously disappear within about 3 months, even if some authors reported the persistence of pillar pain and scar tenderness even after 2 years of follow-up [8]. Endoscopic and limited-incision techniques seem to have fewer complications than classical open surgery, but meta-analysis study was inconclusive on which is the best surgical approach [9]. However endoscopic technique provides faster relief of pain, more rapid improvement in functional abilities and earlier return to work [10].

The nonsurgical interventions with clear benefit are neutral-angle wrist splinting (with a success rate of 37%), and steroids, which show better effects when administered by local injection than orally. The initial positive response rate to injection is 70%, but there are frequent relapses as demonstrated by the 12 studies included in the last Cochrane Review [11].

We have designed a randomised controlled study, realized according to apt criteria for the appraisal of the effectiveness of every new therapeutic strategy, in order to demonstrate the clinical effectiveness of local progesterone in the most frequent human focal peripheral mononeuropathy and the neuroprotective effects at the level of the peripheral nervous system in humans.

## Background

Carpal tunnel syndrome (CTS) results from the compression of the median nerve at the wrist. The typical symptoms are paraesthesiae (numbness, tingling) and pain in the hand distribution of the median nerve, more often occurring during night or in early morning waking up the patients. There may be also sensory loss and hand weakness and clumsiness causing difficulties in daily activities. The prevalence of median nerve symptoms and electrophysiological median neuropathy in the general population of Maastricht was 3.4% for women and 0.6% for men, but another 5.8% of all adult women has undetected CTS [12]. The annual average crude incidence in the Siena area is 329.4/100000 person-years with a highest incidence in range age 50 to 59 years [13].

The severity of CTS ranges from mild to severe. In mild CTS, focal disturbance to myelin is the dominant factor and indeed paranodal demyelination has been documented [14,15], whereas only with more severe nerve compression do demyelination and Wallerian degeneration occur [16,17]. Consequently, patients with mild CTS generally report intermittent symptoms can cause permanent loss of sensation and partial paralysis in abduction and opposition of the thumb, whereas severe CTS can cause permanent loss of sensation and paralysis in abduction and opposition of the thumb.

In conclusion the anti-inflammatory and anti-edema effects of the corticosteroid are limited at 1 month and in CTS present only a symptomatic effectiveness.

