GABA-A involvement in the expression of PMP22 is confirmed by the finding that in cultured rat Schwann cells a specific GABA antagonist such as bicuculline completely abolishes the stimulatory effect exerted by 5α-TH PROG, while an agonist such as muscimol increase this effect [40].

Finally, progesterone is also well known to have anti-inflammatory property, in view of his effects on pro-inflammatory cytokines [41] and prostaglandins [42]; in addition this hormone has demonstrate capability to decrease edema formation after brain injury [43]. By means of these two properties, progesterone could reduce pain in CTS patients, like the cortisone do [44].

The safety of the progesterone in humans has been demonstrated [28,45].

In summary progesterone can to be a therapeutic opportunity in the myelin neuropathy [46] and the mild CTS is a perfect model of the localized myelin damage.

This is a first randomized clinical trial protocol study in humans for the local therapy in CTS: cortisone versus progesterone.

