### Sample size

The main output parameter is the Symptom Severity Scale (SSS) score of the self-administered Boston Carpal Tunnel Questionnaire. The values reported in the literature assessing the cortisone treatment effect after 2 and 3 months are ranging between 1.37 - 2.3 (mean ± standard deviation: 1.6 ± 0.7). It has been estimated that a minimum number of n = 26.2 subjects for each group would be necessary to reveal a significant (α = 0.05) decrease in the SSS score from 1.6 to 2.0 with enough power (90%). If a drop-out of 4 subjects is considered, the minimum number of subjects required should be adjusted to no. = 30.

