### Data analysis

The values for each recorded parameter (NCV, CSA, BQ, VAS) will be submitted to a two-way ANOVA, with the main factors TREATMENT (cortisol vs progesterone) and TIME (baseline, 1 month, 6 months, and 12 months after the injection). The significance level will be set at *p *< 0.05. Tukey's test post-hoc analysis will be performed when necessary, in order compensate for possible type I errors.

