### Design of the trial

Sixty women with idiopathic mild CTS will be evaluated at before (baseline), 1, 6 and 12 months after injection.

The major outcome of this study is to determine that locally-injected progesterone may be more beneficial than cortisone in carpal tunnel syndrome at clinical level (SSS-BQ, VAS). Secondary outcome measures are:

- duration of experimental therapy, with a short (after 1 month) and long follow-up (after 6 to 12 months);

- improvement of electrodiagnostic and ultasonographic anomalies at various follow-up;

- correlation of the neurophysiologic and ultrasonographic data with clinical evaluation;

- comparison of the beneficial and harmful effects of the cortisone versus progesterone.

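### No test or visit is fixed to decide whether progesterone is more beneficial: the TREATMENT main effect would dilute a late advantage, and the TREATMENT × TIME interaction has no direction

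*Protocol article*

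**What the plan says.** The abstract's Methods paragraph states: "The major outcome of this study is to determine whether locally-injected progesterone may be more beneficial than cortisone in CTS at clinical levels". The Design of the trial section repeats this for SSS and VAS. Neither place gives a visit or period.

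The Data analysis section submits each parameter to a two-way ANOVA "with the main factors TREATMENT (cortisol vs progesterone) and TIME", where TIME has four levels: baseline, 1, 6 and 12 months. Tukey post-hoc tests follow if needed. The section names no interaction, primary visit or contrast.

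The rationale is specific about timing for the comparator. The Problem reports that steroid injection beats placebo on symptoms at one month, with no demonstrated relief later, and concludes that "the anti-inflammatory and anti-edema effects of the corticosteroid are limited at 1 month". The Solution adds that "progesterone could reduce pain in CTS patients, like the cortisone do", alongside a distinct myelin-repair action.

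The early/late split appears only under the secondary outcomes, as duration of therapy "with a short (after 1 month) and long follow-up (after 6 to 12 months").

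**The concern.** On the document's own account, cortisone is at its strongest at month 1 and has no demonstrated symptom benefit after that. Month 1 is therefore the post-injection visit with the least reason to expect a progesterone advantage, and 6 and 12 months have the most. Baseline, also a TIME level, precedes treatment and can carry no effect.

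The only between-arm term that the plan names is TREATMENT. Read as the test, it gives all four visits equal weight. Read instead through the interaction, the plan asks whether the arm difference varies over time, which is not the same as asking whether progesterone is better. With Tukey comparisons unspecified, the visit that settles the question could be chosen after the data are seen. A lasting benefit could be missed, or a significant result reported that does not bear on superiority.

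**Working it through.** **Inputs from the document.** Sample size: difference 0.4 (1.6 against 2.0; the text calls this a "decrease in the SSS score from 1.6 to 2.0", and only the size is used here), SD 0.7, α 0.05, 30 per arm. Data analysis: the four TIME levels.

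**Assumptions.** Two-sided test; SD 0.7 at every visit; the same correlation ρ between any two visits, 0.5 with range 0.3–0.7; a repeated-measures model; all 30 women per arm analysed; the 0.4 applied at months 6 and 12. The cortisone values behind the sample size are for 2 and 3 months, which match no visit. Differences are positive when progesterone is better.

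**1. The plan's own figure.** Two groups at 90% power need 2 × (0.7 × (1.960 + 1.282)/0.4)² = 64.4 per arm two-sided, or 52.5 with 1.645 (one-sided). The printed 26.2 comes from the one-sample, one-sided formula (0.7 × (1.645 + 1.282)/0.4)² = 26.2. That is a separate matter; the planned 30 per arm is used below.

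**2. TREATMENT main effect, advantage at 6 and 12 months only.** The variance of a woman's mean over k visits is 0.49 × (1 + (k − 1)ρ)/k, the SE of the arm difference is √(2 × variance/30), and power is from the noncentral t with 58 df.
- Four visits: effect (0 + 0 + 0.4 + 0.4)/4 = 0.20. At ρ = 0.5 the variance is 0.49 × 2.5/4 = 0.306, SE 0.143, ratio 1.40, **power 28%** (35% at ρ = 0.3, 23% at ρ = 0.7).
- Three post-injection visits: effect 0.8/3 = 0.267, variance 0.327, SE 0.148, power 43% (37–51%). Baseline and month 1 each dilute.

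**3. TREATMENT × TIME interaction.** Noncentrality is (30/2) × Σ(deviation from the mean effect)²/(0.49 × (1 − ρ)), with F on 3 and 174 df.
- Progesterone 0.4 better at 6 and 12 months only: Σ = 4 × 0.2² = 0.16; at ρ = 0.5, 15 × 0.16/0.245 = 9.80; **power 74%** (58–93%).
- Cortisone 0.4 better at month 1 only: mean −0.1, Σ = 0.3² + 3 × 0.1² = 0.12; noncentrality 7.35; **rejection 60%** (45–84%).
- Progesterone 0.4 better at all three post-injection visits: mean 0.3, Σ = 0.3² + 3 × 0.1² = 0.12; noncentrality 7.35; **rejection 60%** (45–84%).

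The last two patterns favour opposite arms and give the test identical noncentrality.

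**4. A named late contrast (mean of 6 and 12 months).** Effect 0.40.
- Unadjusted: variance 0.49 × 1.5/2 = 0.3675, SE 0.157, ratio 2.56, **power 71%** (66–77%).
- Adjusted for baseline: variance 0.3675 − 0.5² × 0.49 = 0.245, SE 0.128, ratio 3.13, **power 87%** (83–95%).

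**5. If the benefit were 0.4 at all three post-injection visits.** The three-visit mean has power 76% unadjusted (0.4/0.148 = 2.71). Adjusted, the variance is 0.327 − 0.1225 = 0.204, SE 0.117, ratio 3.43, power 92%.

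**6. Conditional on a month-1 cortisone lead.** A lead of 0.2 reduces the four-visit effect to 0.15 (power 18%); a lead of 0.4 reduces it to 0.10 (10%). It reaches zero only in cases such as cortisone 0.4 ahead at month 1 and progesterone 0.2 ahead at each later visit: (0 − 0.4 + 0.2 + 0.2)/4 = 0.

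**The case against.** The strongest reply is that the article never says superiority is judged on the visit average. Listing main factors describes the model, not the deciding test, and an analysis plan may say more. A two-way ANOVA normally yields the interaction, whose 74% power for the late-only pattern is no worse than the 71% of the unadjusted late contrast. If cortisone led at month 1 by 0.2 or 0.4, interaction power would be 94% or 99.5%. Visit means and post-hoc comparisons could then show direction. This stands in part: the plan as a whole need not miss a late benefit. But a rejected interaction does not say which arm is better, and no post-hoc contrast is named to settle it.

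A reader might go further and infer that month 1 cancels the effect because progesterone can at best match cortisone then. The documents do not support that. The Solution likens progesterone's pain relief to cortisone's without setting a ceiling. It also cites early progesterone actions: myelin repair assessed at 2 weeks, more myelin segments after 4 weeks in culture, and better nerve conduction after 1 month of treatment in diabetic rats. No month-1 deficit is stated, so the leads in step 6 are assumptions only.

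Finally, early relief can legitimately count as benefit, and a contrast confined to 6 and 12 months scores the comparator where its effect is expected to have faded. That is a fair cost of the fix, but not a reason to leave the test unnamed.

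**Conclusion.** The point holds in this form: the article states a superiority question and an analysis, but fixes no term, visit or direction that connects them. If the main effect is the test, a 0.4-point advantage confined to 6 and 12 months is halved and power is about 28% (23–35%). If the interaction is the test, power for that pattern is about 74% (58–93%), but a rejection does not tell a progesterone advantage from a cortisone one. Dilution under the main-effect reading needs only equal arms at month 1; cancellation needs a cortisone lead that the document neither states nor quantifies.

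The sizes rest on the document's 0.4 and 0.7, 30 analysed women per arm, two-sided 0.05, and assumed correlations of 0.3–0.7. With 26 analysed per arm at ρ = 0.5, the main effect, interaction and unadjusted late contrast fall to 25%, 67% and 65%. This is a worthwhile, inexpensive improvement, not evidence that the planned analysis must fail.

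**What to change.** In Data analysis and Design of the trial, name one superiority contrast for SSS, which the Sample size section already calls the main output parameter. It should be the arm difference averaged over 6 and 12 months, adjusted for baseline SSS, with superiority concluded only if the difference is significant and favours progesterone. Align the abstract, and report month 1 as the secondary short follow-up comparison. The ANOVA terms can remain as supporting description.

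The cost is wording only: no new visits or data, and the long follow-up period is already defined. Early relief no longer counts towards the major outcome. If the benefit is equal at all three post-injection visits, power is slightly below that of the three-visit mean: 71% against 76% unadjusted, or 87% against 92% adjusted, at ρ = 0.5. If the sponsor wants early relief to count, the baseline-adjusted three-visit mean is a coherent alternative, provided it is named in advance and its dilution under a late-only benefit is accepted. If an analysis plan already names such a contrast, the article need only be brought into line with it.

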## The Solution

Schwann cells, the myelinating glial cells in the peripheral nervous system, synthesize progesterone in response to a diffusible neuronal signal [24]. In peripheral nerves, the local synthesis of progesterone plays an important role in the formation of myelin sheaths [25,26]. This has been shown in vivo, after cryolesion of the mouse sciatic nerve, and in vitro, in co-cultures of Schwann cells and sensory neurons. After cryolesion axons and their accompanying myelin sheaths degenerate quickly in the frozen zone and the distal segments (Wallerian degeneration). However, the intact basal lamina tubes provide an appropriate environment for regeneration. Schwann cells start to proliferate and myelinate the regenerating fibers after 1 week, and 2 weeks after surgery, myelin sheaths have reached about one third of their final width. In the damaged portion of the nerve, progesterone and pregnenolone (precursor) levels remain high, and even increase 15 days after lesion. The role of progesterone in myelin repair, assessed after 2 weeks, was indicated by the decrease of thickness (number of lamellae) of myelin sheaths when trilostane, an inhibitor of enzyme involved in the pregnenolone to progesterone transformation, was applied to the lesioned nerve. Such an effect was observed in cultures of rat dorsal root ganglia. After 4 weeks in culture, in presence of a physiological concentration of progesterone, the number of myelin segments and total length of myelinated axons are increased enormously.

In addition Schwann cells also express an intracellular receptor for progesterone, which thus functions as an autocrine signaling molecule [27].

Progesterone and its metabolites promote the viability of neurons in the brain, spinal cord and peripheral nervous system. Their neuroprotective effects have been documented in different lesion models, including traumatic brain injury [28], experimentally induced ischemia [29], spinal cord lesions [30,31], and genetic model of motoneuron disease. In experimental diabetic neuropathy [32,33] chronic treatment with progesterone had neuroprotective effects at the neurophysiological, functional, biochemical and neuropathological levels. In this experimental diabetic rats chronic treatment for 1 month with progesterone counteracted the impairment of nerve conduction velocity and thermal threshold, restored skin innervation density, improved Na^+^/K^+ ^ATPase activity and mRNA levels of myelin proteins, such as glycoprotein, peripheral myelin protein 22 (PMP22) and protein zero (P0).

Indeed aging nervous system, that is associated with a reduction in the synthesis of P0 and PMP22, appears to remain sensitive to some of progesterone's beneficial effects [34,35].

Progesterone may promote myelination by activating the expression of genes coding for transcription factors and/or for myelin proteins [36,37] and/or indirectly to regulate myelin formation by influencing gene expression in neurons and may promote neuroregeneration by several different actions by reducing inflammation, swelling and apoptosis, thereby increasing the survival of neurons, and by promoting the formation of new myelin sheaths [27]. Progesterone and its derivates, dihydroprogesterone (5α-DH PROG) and tetrahydroprogesterone (5α-TH PROG), are able to influence the synthesis of myelin proteins under the control of classical receptors (PR, progesterone receptor) and non classical receptors (GABA-A).

PR involvement in the expression of P0 is confirmed by the finding that in cultured rat Schwann cells an antagonist such as mifestone is able to block the stimulatory effect exerted by progesterone and 5α-DH PROG (i.e. classical ligands of PR). This antagonist is also effective in blocking the effect of 5α-TH PROG (i.e. a neuroactive steroid which is able to interact with GABA-A receptor) on P0. Indeed, the activity of the 3α hydroxysteroid dehydrogenase is bi-directional and consequently 5α-TH PROG might be retroconverted into 5α-DH PROG, exerting its effect on P0 via activation of PR [25,38,39].

GABA-A involvement in the expression of PMP22 is confirmed by the finding that in cultured rat Schwann cells a specific GABA antagonist such as bicuculline completely abolishes the stimulatory effect exerted by 5α-TH PROG, while an agonist such as muscimol increase this effect [40].

Finally, progesterone is also well known to have anti-inflammatory property, in view of his effects on pro-inflammatory cytokines [41] and prostaglandins [42]; in addition this hormone has demonstrate capability to decrease edema formation after brain injury [43]. By means of these two properties, progesterone could reduce pain in CTS patients, like the cortisone do [44].

The safety of the progesterone in humans has been demonstrated [28,45].

In summary progesterone can to be a therapeutic opportunity in the myelin neuropathy [46] and the mild CTS is a perfect model of the localized myelin damage.

This is a first randomized clinical trial protocol study in humans for the local therapy in CTS: cortisone versus progesterone.

## Recommendations And Methods

The study is designed as a monocentric randomized clinical trial. The Medical Ethics Committees of the University of Siena approved the study protocol.

### Study population

Patients were enrolled in the study if the symptoms compatible with clinical diagnosis of CTS were confirmed by electrodiagnostic evidence of delay of the distal conduction velocity of the median nerve (for details see respective paragraphs).

Patients who are eligible for participation will be informed about the trial by the neurologist. If they show interest, they will receive written information about the trial with a detailed description of the aim of the study and of the implications of participation. Only subjects able to read, understand and sign the informed consent are included in the study. The information about the trial is also missed to the general practitioner of the patient.

### Clinical criteria

Patients with suspected CTS referred to our electrodiagnostic laboratory to confirm clinical suspicion of CTS will be eligible for including in the trial from 01.06.2008. Patients will be recruited if they will complain at least three months of the following symptoms: nocturnal awaking or activity-related numbness, tingling, burning, pain in the hand distribution of the median nerve according to hand diagram by Katz et al. modified by consensus criteria of classification of the CTS. Only "classic/probable" and "possible" cases will be enrolled [47,48]. Then only patients with "mild" CTS will be successively included in the trial. Mild cases are defined as those patients who complain only symptoms without objective sensory loss, weakness of abduction/opposition of the thumb and hypotrophy/atrophy of thenar eminence, i.e. these patients belonging to stage 1 and 2 of a validated clinical CTS severity scale [49]. Other mandatory inclusion criteria are female gender (because the progesterone is a natural female hormone) and age between 18 and 60 years.

Exclusion criteria are: previous conservative or surgical treatments for CTS, diabetes, connective tissue and thyroid diseases, renal failure, gout, pregnancy, lactation, estrogen drugs, arthritis and deforming arthrosis, onset of CTS symptoms after hand trauma, polyneuropathy, brachial plexopathy, neuropathy of the ulnar nerve at elbow, thoracic outlet syndrome and history of cervical radiculopathy.

Physical examination consisted of evaluating of muscular strength and trophism, sensory function, evocation of deep reflexes and provocative clinical test (Phalen and Tinel signs) will be performed by neurophysiologist before the electrodiagnostic tests.

For subjective evaluation of severity of symptoms, the Boston Questionnaire will be completed by patients just before the injection [50,51]. The questionnaire is divided into two parts. The first part (11 items) evaluates symptoms, and the second part (8 items) evaluates the functional status of the hand. Five answers are possible to each question; they are scored 1 to 5 according to the severity of symptoms or the difficulty of performing a certain activity. Each score is calculated as the mean of the score of individual item. Severe impairment is indicated by a high score.

In addiction visual analogue pain scale (VAS) will be administrated. The patient will be instructed to point to the position on the line between the faces to indicate how much hand pain they are currently feeling. The far left end indicates 'No pain' and the far right end indicates 'Worst pain ever'.

